## Abstract

**Background:**

Poor balance leads to falls, which can cause a loss of personal autonomy and reduced quality of life. Epidemiological studies of balance disorders (BDs) are limited. Identifying their prevalence and accessible diagnostic markers is crucial for prevention and monitoring.

**Aims:**

1) Assess the prevalence of BDs in men and women aged 65–72 using posturography and different balance tests, and track the annual incidence of BD; 2) Analyze the association between retinal microvasculature abnormalities and BD; 3) Evaluate the effectiveness of the Wii Balance Board™ for balance assessments compared to posturography; 4) Explore whether knee extensor strength and a combined measure of physical and cognitive function can serve as predictors for BD and fall risk: and 5) Conduct an external validation of the Health Assessment Tool (HAT) in the Spanish population.

**Methods:**

Two-phase, observationals study. Phase I: Descriptive, cross-sectional. Phase II: Follow-up of cohorts at 18 months. Sample: 1,316 people aged 65–75 residing in Mataró (Barcelona, Spain) shall be included in the study, excluding individuals who cannot walk independently. They shall undergo posturography, retinal photography, knee extensor strength assessment, as well as the Tinetti Test, Timed Up and Go test, Unipedal stance test, Short Physical Performance Battery (SPPB), and balance assessment using the Nintendo Wii at baseline and at the end of the follow-up period. Bimonthly phone calls shall be made to detect the occurrence of falls.

**Applicability and relevance:**

BDs are underdiagnosed and under-treated, and current awareness only scratches the surface. Expanding knowledge in this field is essential to avoid the loss of functional autonomy in individuals. Doing so will make it possible to develop specific preventive measures for the population at greatest risk of falls, thus making the approach to this significant geriatric syndrome more efficient.

The EPIBAS study is registered on Clinicaltrials.gov under the code NCT06965660.

## Introduction

The aging process is accompanied by a decline in several body functions involved in maintaining balance. Poor balance and gait disorders lead to falls, resulting in a loss of personal independence, reduced quality of life [1], stress, isolation, and decreased physical activity [2]. Injuries from falls, defined as unintentional loss of balance leading to failure of postural stability, can result in extended use of healthcare services and high healthcare costs [3,4]. There is a pressing need to anticipate falls and understand the prevalence of balance disorders (BDs) to offer rehabilitation treatments or preventive strategies for those at most risk.

Previous studies indicate that balance, as an independent factor, is associated with survival, the better the balance, the longer the survival [5,6]. Impaired proprioception, visual loss, peripheral polyneuropathy, strokes, loss of muscular strength, and vascular diseases are common causes of gait and BD in the elderly [3,7,8]. Instability in older adults may be related to the specific impairments in these systems or cumulative loss of function associated with age. This multifactorial etiology, with diverse treatments, makes it difficult to determine and address the underlying cause.

Epidemiological studies on BS are limited [9,10] and often rely on patient series to estimate prevalence. One of the most recent studies, conducted in Turkey [11], used the Berg Balance Scale and reported that 34% of elderly participants experienced BDs. Another study from the USA based its findings on self-reported survey data [12]. Literature reports a prevalence of dizziness of 3–7% in the general population, with instability rising to 17–30%. Prevalence is even higher between 65 and 69 years, reaching over 40% for adults aged 80–84 [13]. Only one epidemiological study in Spain has investigated BD prevalence at the population level in primary care [14], but it does not assess the prevalence of presbyequilibrium, the natural involution of the balance system due to aging, causing slight vestibular symptomatology and moderate disability [15].

In the context of the demographic transition towards a progressively aging population, it is essential to determine the prevalence and incidence of BDs and describe potential markers for easy detection and monitoring. Simple and practical tools are needed at the population level to identify individuals with BD, such as measuring retinal vasculature, an indirect marker of brain vascular disease, with non-mydriatic cameras, and using balance platforms like the Wii Balance Board™.

Some studies describe a correlation between postural instability (measured by unipedal stance time) and asymptomatic cerebral microcirculation abnormalities (lacunar stroke, periventricular hyperintensities, and microhemorrhages) detected through Magnetic Resonance Imaging (MRI) [16–19] in healthy adults, potentially representing an early biomarker for cognitive decline. The ocular fundus offers a window to observe the circulatory system. Findings in retinal microcirculation predict functional decline and slowed gait in older adults [20], reflecting the status of the cerebral vascular tree [21] and serving as biomarkers for cerebral infarcts, strokes, and white matter lesions [22].

The retina can be considered an extension of the brain; in embryological terms, the retina is an extension of the diencephalon. There is evidence of an association between retinal vessel density and cognition as measured by MoCA in healthy older adults [23]. Examining the retina with non-mydriatic cameras is a widely employed technique in primary care since it is quick, safe, and non-invasive and allows direct observation of the ocular fundus and retinal microcirculation. A study performed on a Catalan cohort allowed researchers to describe abnormalities detected in the arteriovenous (A/V) ratio in retinal microcirculation using images taken with a non-mydriatic retinal camera as potential biomarkers of silent cerebral ischemia [24]. It is feasible that cerebral microcirculation abnormalities affect the postural balance system, and there may be a relationship between postural balance markers and cerebral microcirculation markers observed in the retina. These findings underscore the importance of retinal vasculature assessment as a tool for the early detection of cerebrovascular disease.

Balance platforms are suitable for taking specialized measurements and use in postural balance rehabilitation. However, their high cost and the challenges of transportation and management make them less practical for clinical and community settings. Various studies reveal there is an acceptable correlation between the Wii Balance Board™ and force balance platforms used for Posturography, which are considered the laboratory gold standard. However, a systematic review carried out by Clark et al. identifies some limitations in the use of the Wii Balance Board™ to assess balance in clinical settings [25]. Our group performed a clinical trial to evaluate whether using the Wii Balance Board™ could improve balance, reduce falls, or improve fear of falling [26]. It yielded positive results regarding fear of falling after participants had completed a training program.

Aging affects individuals differently, leading to varying health trajectories impacting healthcare systems and individual needs. Tools that help detect the most susceptible or at-risk subjects are invaluable, and the Health Assessment Tool (HAT) appears to be one of them [27]. HAT is a simple index for assessing individuals’ clinical and functional status, allowing early detection of health changes and prediction of the care needs of older people. Developed and validated based on the Swedish National Study on Ageing and Care (SNAC), HAT presents the advantage of not having any floor or ceiling effect. It is based on five clinical indicators: physical function (walking speed), cognitive function (Mini-Mental State Examination [MMSE]), number of chronic disorders, dependence on instrumental activities of daily living (IADL), and personal activities of daily living (ADL).

Previous studies highlight the need to validate the HAT tool in other populations [28]. We aim to test HAT’s ease of use, feasibility, and predictive performance concerning BD and presbyequilibrium in a Spanish cohort of older adults. BDs are a frequent reason for consultation in primary care [14], but they do not receive the attention they deserve due to a lack of resources or knowledge on how to proceed. This study aims to provide objective data on the prevalence and incidence of this problem in our community to plan future preventive interventions.

## Study rationale and hypotheses

The aging process is accompanied by a decline in several body functions involved in maintaining balance. Poor balance and gait disorders lead to falls, resulting in a loss of personal independence and reduced quality of life. Despite the significant impact of injuries from falls and their associated healthcare costs epidemiological studies on balance disorders (BDs) are limited, and current awareness only scratches the surface. There is a pressing need for accessible diagnostic markers and simple, practical tools in primary care – such as retinal microvasculature assessment, the Wii Balance Board™, and the Health Assessment Tool (HAT) – to identify individuals at risk and provide early preventive strategies. Hence, the main hypotheses stated in this study are: 1) The presence of BD, objectively measured by posturography, is associated with an increased risk of falls and worse fall-related functional outcomes in the general population, compared to individuals without such disorders; 2) Cerebral microcirculation abnormalities and early structural alterations in the brain may impact the postural balance system. These can potentially be measured through the observation of retinal microvasculature using non-mydriatic camera images of the ocular fundus; 3) Measurements of balance using the Wii Balance Board™, knee extensor strength, retinal microvasculature abnormalities, and the comprehensive Health Assessment Tool (HAT) may predict the incidence of BD, the resulting risk of falls, and the subsequent use of Health services in adults aged 65 and over.

Providing objective data on the prevalence and incidence of this problem is essential to plan future preventive interventions. Identifying individuals at the greatest risk will allow for the development of targeted fall prevention and rehabilitation programs, ultimately helping to reduce the loss of autonomy and enhance the quality of life for the elderly population.

## Study aims

*Primary aims*

Determine the prevalence of BD assessed using posturography in a cohort of men and women aged 65–75, and track the annual incidence of BD at an 18-month follow-up.Analyze the association between retinal microvasculature abnormalities, observed in retinal photographs, and the markers of BD detected through posturography.Analyze the validity of balance assessments taken with the Wii Balance Board™ in comparison to posturography, the current gold standard method.Determine whether measurements of knee extensor strength and a composite measure of physical and cognitive function can predict BDs and fall risk.

*Secondary aims*

Conduct an external validation of the Health Assessment Tool (HAT) in the Spanish population.

## Methods

### Study design

This study will be performed and reported according to the Strengthening the Reporting of Observational Studies in Epidemiology Criteria (STROBE) [29].

This is a two-phase, observational study:

Phase 1: A descriptive, cross-sectional study on the prevalence of BDs in individuals aged 65–72.

Phase 2: A longitudinal, population-based cohort study to determine the occurrence of postural BDs and their consequences over an 18-month follow-up period in individuals aged 65–72. The potential consequences include: a) Falls: Defined as involuntary events in which an individual loses their balance and ends up on the floor or another hard surface. b) Fall-related consequences: Including contusions, fractures, hospitalization, and death.

Based on the above-mentioned cohort data, the external validation of the HAT scale will be performed by analyzing its predictive capacity for BDs and the use of health services after 18 months of follow-up (hospital admissions, 30-day readmissions, days spent in the hospital, primary care visits, and specialist care visits).

### Setting

The study is set in primary care, targeting people aged 65–75 living in Mataró (Barcelona, Spain).

### Participants

The target population is an age-based cohort of people aged 65–75 living in Mataró. This age range was selected to find individuals who do not yet have BDs, enabling the calculation of the incidence. According to the 2017 municipal register, and the population’s age structure, there are 2,215 people in this age range. A total of 1,316 people will be randomly selected from the Primary Care Information System (SIAP) database, which includes health cardholders and covers nearly the entire population. The selection process will be conducted using a computer-generated random sequence to form a sample stratified by gender and age. Our research team will contact the selected participants using the phone numbers registered in the SIAP and invite them to participate. To ensure robustness and minimize non—response bias, a protocol of up to six call attempts on different days and at different times will be implemented for each candidate before considering them unreachable.

Eligibility criteria: 1) Aged 65–75 years at the time of recruitment. 2) Resident of Mataró (Barcelona, Spain) and registered in the Primary Care Information System (SIAP). 3) Able to walk independently, defined as the ability to walk at least 10 meters without the assistance of another person, although the use of technical aids (e.g., cane, walker) is permitted.

Exclusion criteria: 1) Permanent inability to walk or requirement of human assistance for mobility. 2) Terminal illness, as a document in the primary care electronic medical record. 3) Severe cognitive decline, as assessed by the Pfeiffer questionnaire or Mini-Mental State Examination (MMSE) during the initial evaluation, or a known diagnosis of advanced dementia. 4) Significant language barrier that prevents the completion of clinical scales or understanding of study procedures. 5) Lack of phone access for follow-up calls.

### Sample size

We expect 33% of the target population (2,215 subjects) to present a BD at recruitment. In Spain, between 14% and 46% of adults aged 65 and over experience one fall per year [30]. In the worst-case scenario, if the cohort with BDs has a fall incidence of 50%, to determine a risk ratio of 1.3 compared to the group without BDs, the latter group’s incidence would need to be around 38.5%. Accepting an alpha risk of 5% and a beta risk lower than 20%, with a dropout rate of 20% at follow-up, 329 subjects would be needed in the BD group and 987 in the non-BD group to detect a minimum risk ratio of 1.3 (objective 2). This total sample of 1,316 subjects allows for determining a prevalence of falls of 50% with ±2.7% precision (objective 1).

Regarding the retinal A/V ratio, a previous study on hypertensive patients observed a prevalence of pathological A/V ratio of 15% [21]. Given that at least 75% of the Spanish population presents with hypertension. Therefore, of the total cohort of 1,316 individuals, we expect 148 to show a pathological A/V ratio. If 33% of the population is expected to have BDs, in this sample of 148 individuals, a prevalence of 12.5% in patients with a normal A/V ratio will represent a significant difference (aim 2).

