A two-sided p-value <0.05 will be considered statistically significant. All analyses will be performed using SPSS version 23.0.

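### A 50% fall incidence is not the worst case for detecting a risk ratio of 1.3: power falls at lower incidence and is below 80% in the lower part of the plan's own 14–46% per year range

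*Protocol article*

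**What the plan says.** All of the sizing is in the Sample size section of the protocol article. It first gives a background range for Spain: "between 14% and 46% of adults aged 65 and over experience one fall per year". It then sets the design point: "In the worst-case scenario, if the cohort with BDs has a fall incidence of 50%, to determine a risk ratio of 1.3". For the group without BD, the "incidence would need to be around 38.5"%.

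The error rates are given as "Accepting an alpha risk of 5% and a beta risk lower than 20"%, "with a dropout rate of 20% at follow-up". The result is that "329 subjects would be needed in the BD group and 987 in the non-BD group", in order "to detect a minimum risk ratio of 1.3 (objective 2"). The same section expects 33% of the target population to have a BD. It also uses 50% for the ±2.7% precision of a single prevalence.

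The Statistical analysis section fixes the outcome as at least one fall over 18 months, analysed by modified Poisson regression with relative risks and 95% confidence intervals. The test is two-sided: "A two-sided p-value <0.05 will be considered statistically significant".

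**The concern.** A proportion of 50% is the least favourable value for the confidence interval of one proportion, so the label suits the ±2.7% figure. The sentence attaches it to the risk-ratio calculation instead. There the effect is held fixed as a ratio, and the direction reverses.

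Writing p0 for the non-BD risk, a ratio of 1.3 means an absolute difference of 0.3 × p0. The squared difference shrinks with p0², while the variance shrinks roughly with p0(1 − p0). The signal therefore behaves like p0/(1 − p0) and weakens as falls become rarer.

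A reader told that the calculation is worst-case will take beta below 20% to be secured at any lower incidence. BD and falls is the first hypothesis in the Study rationale, and this is the only comparison in the section given an explicit alpha, beta and dropout. If falls are uncommon in this cohort, its stated sensitivity is too optimistic.

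**Working it through.** **Inputs.** From Sample size: risk ratio 1.3; 50% versus 38.5%; 329 and 987 participants; 20% dropout; 33% expected BD prevalence; 14–46% falling per year. From Statistical analysis: 18-month outcome, two-sided 5%. Completers are 329 × 0.8 = 263 and 987 × 0.8 = 790 (25:75). At 33% prevalence they are 1,316 × 0.33 × 0.8 = 347 and 1,316 × 0.67 × 0.8 = 705 (33:67).

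**Formula.** Two-proportion normal approximation: power = Φ[(d − 1.96·s0)/s1]. Here d = p1 − p0, s0² = p̄(1 − p̄)(1/n1 + 1/n0) with p̄ the pooled risk, and s1² = p1(1 − p1)/n1 + p0(1 − p0)/n0.

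**Step 1: the plan's own figure.** 0.50/1.3 = 0.385. The matching sample-size formula with a 1:3 split gives 259 BD completers at 90% power. 259/0.8 = 324, and 3 × 324 = 972, total 1,296, within 2% of 1,316. At exactly 80% power it gives 193, inflated to 242 and 726, which does not match. The stated numbers thus correspond to beta of about 10%, consistent with a beta below 20%. Directly, with 263 and 790: d = 0.115, s0 = 0.0351, s1 = 0.0354, and (0.115 − 0.0687)/0.0354 = 1.31, so power is about 90% (91% with the ratio held at exactly 1.3).

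**Step 2: ratio fixed at 1.3, lower 18-month non-BD risk (263:790).**
- 30% versus 39%: (0.090 − 0.0652)/0.0342 = 0.72, power 77%.
- 20% versus 26%: (0.060 − 0.0573)/0.0306 = 0.09, power 53%.

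**Step 3: where power reaches 80%.**
- 25:75: non-BD risk 31.7%, BD risk 41.3%. Cohort risk = 31.7% × (1 + 0.25 × 0.3) = 34.1% over 18 months.
- 33:67: non-BD risk 28.6%, BD risk 37.1%. Cohort risk = 28.6% × (1 + 0.33 × 0.3) = 31.4%.

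**Step 4: put the quoted range on the 18-month scale.** The range is annual and describes older adults as a whole, so it must be converted before comparison. Assuming a constant hazard (the documents give no conversion), the 18-month risk is 1 − (1 − annual)^1.5. In reverse, 1 − (1 − 0.341)^(2/3) = 24% per year, and 1 − (1 − 0.314)^(2/3) = 22% per year.

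At 14% per year, 1 − 0.86^1.5 = 20.2%. With 25:75 the non-BD risk is 20.2%/1.075 = 18.8% and the BD risk 24.5%. Then (0.0565 − 0.0561)/0.0299 = 0.01, power 51%. With 33:67 the risks are 18.4% and 23.9%, power 55%.

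**Step 5: detectable ratio.** For each row the cohort risk c is held fixed, p0 = c/[1 + f(RR − 1)] with f the BD share, and RR is solved for 80% power.

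| Annual cohort incidence | 18-month cohort risk | Power for RR 1.3 (25:75 / 33:67) | RR detectable at 80% power (25:75 / 33:67) |
|---|---|---|---|
| 14% | 20.2% | 51% / 55% | 1.45 / 1.42 |
| 20% | 28.4% | 69% / 74% | 1.35 / 1.32 |
| 24% | 33.7% | 79% / 84% | 1.30 / 1.28 |
| 30% | 41.4% | 91% / 94% | 1.25 / 1.24 |
| 46% | 60.3% | above 99% / above 99% | 1.17 / 1.16 |

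**The case against.** The strongest defence is that the design is reasonable and its inputs are open. The sentence is conditional and prints both 50% and 38.5%. The sample size reproduces with slack, at about 90% rather than 80% power. On the 18-month scale, 30% per year, the midpoint of the quoted range, gives a cohort risk of 41.4% and a non-BD risk of 38.5%, which is the plan's own design point. Power is below 80% only in roughly the lowest quarter to third of the range: (22.2 − 14)/32 = 26% of it, or (24.3 − 14)/32 = 32%. The analysis will report relative risks with 95% confidence intervals, so an imprecise null result would show its imprecision.

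All of this stands and limits the severity. It does not rescue the label, which asserts that lower incidences are covered when they are not.

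Four stronger readings are tempting, and the documents do not support them:
- **That the sample size is an arithmetic error.** Step 1 reproduces it.
- **That power falls to 38% (or 43% with 33:67) at the bottom of the range.** That treats 14% per year as an 18-month non-BD risk. The range is annual and for the whole population; on the outcome's scale the bottom is about 51% or 55%.
- **That 50% lies above the plan's own range.** It exceeds 46%, but 46% per year is 60.3% over 18 months, so an 18-month risk of 50% is not outside it.
- **That a null result will be taken to exclude a ratio of 1.3.** No section plans that interpretation.

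**Conclusion.** The point holds as a mislabelled assumption that overstates power, of moderate severity. With the ratio fixed at 1.3, 50% is a mid-range design value and not the worst case. Beta below 20% holds only if the 18-month non-BD fall risk is at least about 32% (25:75) or 29% (33:67). That corresponds to about 24% or 22% per year in the cohort, and the quoted range extends down to 14%.

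The conclusion rests on an unadjusted two-proportion approximation, the plan's 20% dropout, reading the quoted range as the share of people who fall in a year, and a constant hazard for the conversion to 18 months. The direction does not depend on these choices. Even with no dropout at all (329:987), power is below 80% for an 18-month cohort risk under about 29%, and 14% per year converts to 20%. The mismatch between the 25% BD share in the group sizes and the expected 33% is a separate matter. Both splits are shown, and neither restores 80% power at the low end.

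**What to change.** In Sample size, delete the worst-case wording from the risk-ratio sentence and present 50% versus 38.5% as a design assumption, with its power of about 90%. Then state the condition: after 20% dropout, a risk ratio of 1.3 is detectable with at least 80% power only if the 18-month non-BD fall risk is at least about 32% (25:75) or 29% (33:67).

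Add the detectable ratio across the quoted range, converted to 18 months with the constant-hazard assumption stated. By annual cohort incidence (25:75 / 33:67): 14%, 1.45/1.42; 20%, 1.35/1.32; 24%, 1.30/1.28; 30%, 1.25/1.24. Do not enter 14% as though it were an 18-month risk. When the results are reported, read the confidence interval for the relative risk against this table at the incidence observed.

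The cost is one reworded paragraph and a short table, with no extra participants. The price is a claim that becomes conditional and less favourable. The Study status section says no analysis has begun, so the change can be made before results are known.
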